## Abstract

**Methods::**

This is a prospective, randomized, double-blind, placebo-controlled trial to study the efficacy and safety of Xuefu Zhuyu Granules combined with Western medicine in the treatment of angina pectoris of coronary heart disease. Participants will be randomly divided into a treatment group or a control group, and all patients will receive Western medicine treatment based on guideline recommendations. On this basis, the treatment group orally takes Xuefu Zhuyu Granules and the control group orally takes Xuefu Zhuyu Granules mimic, and are followed up for 24 weeks after 12 weeks of continuous treatment. The observation indexes include: cardiac function parameters (left ventricular end-diastolic diameter; left ventricular end-systolic diameter; left ventricular ejection fraction, blood lipid levels (total cholesterol; triacylglycerol; low-density lipoprotein cholesterol; high-density lipoprotein cholesterol), the number of angina attacks per week, total amount of nitroglycerin tablets taken, and adverse reactions. Finally, SPSS22.0 (IBM Company, New York, NY) software will be used for statistical analysis of the data.

**Discussion::**

This study will evaluate the efficacy and safety of Xuefu Zhuyu Granules combined with Western medicine in the treatment of angina pectoris of coronary heart disease. The results of this study will verify whether the efficacy of Xuefu Zhuyu Granules in the treatment of angina pectoris of coronary heart disease belongs to the placebo effect, which will also provide a reference for the clinical use of Xuefu Zhuyu Granules as a supplementary scheme for the treatment of angina pectoris of coronary heart disease.

## 1. Introduction

Coronary heart disease is one of the most common chronic diseases worldwide.^[1]^ According to statistics, 17.9 million people died of cardiovascular diseases worldwide in 2016, of which about 34% died of coronary heart disease.^[2,3]^ Angina pectoris is the most important and common type.^[4]^ It is a syndrome caused by acute myocardial ischemia and hypoxia.^[5]^ Studies have shown that angina pectoris of coronary heart disease is not treated in time, about 30% of patients will develop myocardial infarction, a serious threat to the life safety of patients.^[6]^ According to guidelines for the prevention and treatment of coronary heart disease, nitrates, β-blockers, calcium channel blockers, anticoagulants, and lipid-lowering drugs are standard and first-line therapeutic drugs for angina pectoris in coronary heart disease.^[7,8]^ Although these drugs rapidly improve clinical symptoms, there are some limitations in the face of the complex disease of coronary heart disease angina pectoris.^[9]^ And clinical studies have found that traditional anti-myocardial ischemia therapy does not reduce the incidence of cardiovascular adverse events, and 5% to 15% of refractory patients still have angina pectoris symptoms.^[9,10]^ Therefore, new treatment regimens are needed for the treatment of angina pectoris in coronary heart disease.

An important cause of angina pectoris in coronary heart disease is narrowing of small blood vessels supplying blood and oxygen to the heart,^[11]^ which is consistent with the Qi stagnation and blood stasis theories of traditional Chinese medicine.^[12]^ Therefore, regulating Qi and promoting blood circulation is the main therapeutic goal. Xuefu Zhuyu Granules is a traditional Chinese medicine prescription derived from the Qing Dynasty in China and has the effect of promoting Qi and activating blood circulation.^[13]^ Experimental studies have found that the potential mechanism of Xuefu Zhuyu Granules in the treatment of angina pectoris of coronary heart disease includes improving cardiac energy supply, reducing phospholipid peroxide, maintaining the polyunsaturated fatty acid metabolic peroxide balance and regulating amino acid metabolism, which has the effect of lowering blood lipids and whole blood viscosity.^[14]^ Xuefu Zhuyu Granules can greatly improve skin blood perfusion and improve the prognosis of patients with stable coronary heart disease.^[15]^ In China, the combination of traditional Chinese medicine and Western medicine is common, and such a treatment regimen can exert their respective advantages of traditional Chinese medicine and Western medicine to enhance the efficacy and reducing adverse reactions.^[16]^ The latest systematic review showed that Xuefu Zhuyu Decoction combined with Western medicine has advantages in the treatment of coronary heart disease, but its quality of evidence is low.^[17]^ Due to the lack of double-blind, placebo-controlled clinical studies, it remains controversial whether the efficacy of Xuefu Zhuyu Decoction is a placebo effect, and whether it has a synergistic effect and is safer in combination with Western medicine. This study will explore the efficacy and safety of Xuefu Zhuyu Granules combined with Western medicine for the treatment of angina pectoris of coronary heart disease through a prospective, randomized, double-blind, placebo-controlled trial.

## 2. Materials and Methods

### 2.1. Study design

This is a prospective, randomized, double-blind, placebo-controlled study to explore the efficacy and safety of Xuefu Zhuyu Granules combined with Western medicine for the treatment of angina pectoris of coronary heart disease. Participants will be randomly divided into the treatment group and the control groups. Under the recommendation based on the guidelines, patients in both groups will receive a standard Western medicine treatment scheme. On this basis, the treatment group will receive Xuefu Zhuyu Granules orally, and the control group will receive Xuefu Zhuyu Granules mimic orally, follow up for 24 weeks after 12 weeks of continuous treatment. Flow diagram is shown in Figure 1, and study schedule is shown in Table 1. This study will follow the latest Consolidated Standards of Reporting Trials (CONSORT 2017)^[18]^ and Standard Protocol Items: Recommendations for Interventional Trials (SPIRIT checklist) 2013 statement.

**Table 1 T1:** Study schedule.

Project	Stage				
	Screening period	Treatment period	Follow-up		
	Baseline	12-week	6-week	12-week	24-week
Record fill	√				
Fulfill inclusion criteria and exclusion criteria	√				
Sign informed consent	√				
Random allocation	√				
Treatment	√	√			
**Effectiveness observation**					
Cardiac function indexes	√	√	√	√	√
Blood lipid levels	√	√	√	√	√
Number of angina attacks per week	√	√	√	√	√
Total amount of nitroglycerin tablets	√	√	√	√	√
**Safety evaluation**					
Vital signs	√	√			√
Blood test and urinalysis	√	√			√
Liver and kidney function	√	√			√
Record of adverse event		√	√	√	√

**Figure 1. F1:**
[figure not shown]
Flow diagram.

### 2.2. Ethics and registration

The study protocol will be conducted in accordance with the Declaration of Helsinki and Ethical Guidelines for Clinical Research. This study has been reviewed by the Clinical Research Ethics Committee of our hospital and registered on the Thai Clinical Trials Registry (registration number: TCTR20220906002). Before randomization, all patients will be asked to sign an informed consent form, and they can choose whether to continue the trial at any time.

### 2.3. Sample size

The estimation of sample size is based on the mean and standard deviation of the scores of the left ventricular ejection fraction of patients after 12 weeks of treatment. Referring to the results of the preliminary experiment, 54.74 ± 11.17 in the treatment group and 48.58 ± 10.98 in the control group. Setting *α* = 0.05, using the different test, *β* = 0.20. It is calculated by PASS15.0 (NCSS Company, Kaysville, UT) software that 41 participants are needed in each group, with an estimated dropout rate of 20%, 52 patients will be included in each group.

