### 2.10. Statistical analysis

Outcome measure data will be statistically analyzed by the full analysis set and per-protocol set. Safety evaluation data will be based on safety set. Statistical evaluation of full analysis set will follow intent-to-treat. Data from this study will be statistically analyzed using SPSS22.0 (IBM Company, New York, NY) software. Count and grade data will be expressed as percentage (%), 2-test or non-parametric test; measurement data will be expressed as mean ± standard deviation or interquartile range M (P25, P75), normal distribution will be analyzed by *t*-test, and skewed distribution will be analyzed by non-parametric test; If the data at multiple time points are normal and have homogeneous variance, the analysis of variance will be used, otherwise the generalized estimating equation will be used; The difference will be considered statistically significant when *P <* .05.

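### The 41 per group reproduces only for an undeclared one-sided 5% test; under the conventional two-sided reading, power after the assumed 20% dropout is about 70%, not 80%

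*Protocol article*

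**What the plan says.** Section 2.3 (Sample size) bases the calculation on "the left ventricular ejection fraction of patients after 12 weeks of treatment". Its inputs come from a preliminary experiment: "54.74 ± 11.17 in the treatment group and 48.58 ± 10.98 in the control group". The error rates are introduced with "Setting *α* = 0.05, using the different test", and β is set at 0.20. The result, obtained with PASS 15.0, is that "41 participants are needed in each group, with an estimated dropout rate of 20%, 52 patients will be included in each group".

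Section 2.5 fixes 1:1 allocation. Section 2.10 (Statistical analysis) plans a t-test for normally distributed measurements, a non-parametric test for skewed ones, a test for counts (evidently chi-square, with its symbol lost in the text), and analysis of variance or generalized estimating equations for repeated time points. It closes with a single criterion: "The difference will be considered statistically significant when" P is below .05. Neither section says whether tests are one-sided or two-sided.

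**The concern.** The sample-size statement is complete enough to be recalculated: means, standard deviations, α, β, allocation, number needed, dropout and number enrolled are all given. When it is recalculated for the test a reader would expect from section 2.10, the number needed is 52 per group, not 41. That 52 coincides with the number to be enrolled, so the allowance for dropout would be used up before anyone drops out.

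The stated power is at stake. If a 6.16-point LVEF difference is real and the assumed dropout occurs, a two-sided test would miss it about 30% of the time, against the 20% in the plan. The Discussion part of the Abstract says that the results will verify whether the treatment's efficacy is a placebo effect. A trial with that aim needs its chance of a false negative stated correctly.

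**Working it through.** **Inputs** (section 2.3; allocation from section 2.5)
- Difference: 54.74 − 48.58 = 6.16 points.
- Pooled SD: √[(11.17² + 10.98²)/2] = √122.66 = 11.075.
- Standardized difference: 6.16/11.075 = 0.556.
- α = 0.05, power = 0.80, two equal groups.

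**Step 1: reproduce the 41.** The normal approximation is n = 2(z₁ + z₂)² × SD²/difference², with z₂ = 0.8416 for 80% power.
- One-sided 5% (z₁ = 1.6449): 2 × (2.4865)² × 122.66/37.95 = 39.97, so 40.
- Two-sided 5% (z₁ = 1.9600): 2 × (2.8016)² × 122.66/37.95 = 50.75, so 51.

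The exact power of the t-test uses the noncentral t distribution with 2n − 2 degrees of freedom and noncentrality 6.16/(11.075 × √(2/n)):

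| Per group | One-sided 5% | Two-sided 5% |
|---|---|---|
| 40 | 79.4% | 69.0% |
| 41 | **80.3%** | **70.1%** |
| 51 | 87.4% | 79.4% |
| 52 | 87.9% | **80.2%** |

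The smallest number reaching 80% is 41 one-sided and 52 two-sided. Using 11.17 or 10.98 in place of the pooled SD moves the two-sided answer only between 51 and 53. Rank-test versions give 54 to 60. No two-sided variant tried gives 41.

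**Step 2: the dropout step.** 41/(1 − 0.20) = 51.25, rounded up to 52. This step is done correctly.

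**Step 3: power of the trial as enrolled, two-sided 5%.**
- All 52 per group evaluable: 80.2%.
- 41 per group evaluable, as planned after 20% loss: 70.1%. Across the SD choices and both formulas, the range is 69.4% to 71.9%.
- 42 per group evaluable (52 × 0.8 = 41.6, rounded up): 71.2%.

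**Step 4: detectable difference, two-sided, 41 per group, 80% power.** Noncentral t gives 6.94 points. The normal approximation, 2.8016 × 11.075 × √(2/41) = 6.85, is slightly too favourable. Both exceed 6.16.

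**Step 5: size needed without adjustment.** 52/(1 − 0.20) = 65 per group, 130 in total instead of 104.

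**Step 6: effect of baseline adjustment.** Adjusting for baseline LVEF multiplies the residual variance by 1 − ρ², where ρ is the within-group correlation between baseline and week 12. For 41 adjusted patients to do the work of 52 unadjusted ones, 1 − ρ² must be at most 41/52 = 0.788, so ρ must be at least √0.212 = 0.46. The documents give no value of ρ, so a margin is sensible: about 0.46 to 0.47.

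**The case against.** **Sidedness is inferred.** This is the strongest objection, and it stands as a limit on the claim. Section 2.3 says only "using the different test" and section 2.10 gives only a P-value threshold. A reader might infer that the article plans two-sided tests and that 80% power is therefore simply false. The documents do not support that much: two-sided is the conventional reading, not a documented choice. Since 41 is exactly the one-sided t-test answer, a one-sided calculation was probably run. If the analysis were also meant to be one-sided, 41 would be right and the defect would be non-declaration.

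This does not remove the point. Nothing in the article announces a one-sided test, and the same criterion governs chi-square, analysis of variance and generalized estimating equations, which are ordinarily non-directional. The article needs correction under either reading.

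**The week-12 t-test may not be the only efficacy analysis.** LVEF is also measured at baseline and three follow-up visits, and a repeated-measures model could have different power. That is fair, and the 70% applies to an unadjusted week-12 comparison. That comparison is, however, the one on which section 2.3 bases the size.

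**The full dropout may not occur.** Also fair: with no loss, two-sided power is 80.2%. But the plan itself assumes 20%. The intent-to-treat wording in section 2.10 does not bring back information lost with missing week-12 LVEF.

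**A non-significant result might be read as evidence against the treatment.** A reader might infer this from the stated aim, but it is a prediction about interpretation. The Abstract says only what the results are meant to verify.

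**Conclusion.** Wrong as written. The stated inputs give 41 per group only for a one-sided 5% t-test that is declared nowhere. On the conventional two-sided reading, 52 evaluable per group are needed and the 52 enrolled carry no dropout allowance. The power shortfall ranges from nothing, if no one is lost, to about 10 percentage points at the assumed 20% loss.

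This rests on three assumptions: two-sided testing, which the documents do not state; an unadjusted week-12 LVEF comparison; and missing LVEF for those who drop out. The arithmetic itself is firm, and the choice of SD or formula does not explain the gap. A reader might also suspect the dropout inflation, but that step is correct.

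**What to change.** 1. In sections 2.3 and 2.10, state that tests are two-sided at 5%.
2. In section 2.3, restate the figure along these lines: *52 randomised per group, about 41 evaluable after 20% dropout, give about 70% power (80% only with no dropout) for a 6.16-point difference in week-12 LVEF.*
3. In addition, specify the week-12 LVEF comparison as adjusted for baseline LVEF (analysis of covariance). Baseline LVEF is already in the study schedule. State the assumed correlation and its source; at 41 per group, 80% power needs at least about 0.46 to 0.47.

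The cost is rewording, and a less favourable power statement unless adjustment is adopted and the correlation can be justified. No patients are added. If the sponsor wants 80% power without relying on an assumed correlation, the alternative is 65 per group, 26 more patients in total (130 − 104).

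If a one-sided 5% test was truly intended, the 41 and 52 may stay, but both sections must declare the one-sided test.

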### 2.4. Patients

#### 2.4.1. Diagnosis basis.

The diagnostic criteria for angina pectoris of coronary heart disease refer to the Nomenclature and Criteria for Diagnosis of Ischemic Heart Disease formulated by the World Health Organization.^[19]^ Traditional Chinese medicine (TCM) diagnostic criteria refer to the Diagnostic and Therapeutic Criteria for TCM diseases.^[20]^

#### 2.4.2. Inclusion criteria.

Meet the diagnostic criteria of coronary heart disease angina pectoris in traditional Chinese medicine and Western medicine, coronary angiography or coronary angiography showed at least one coronary artery stenosis and catheter stenosis ≥50%.Aged ≥18 years old, and ≤70 years old.Canadian Cardiovascular Society classification of angina pectoris is grade I–III.Angina pectoris attack frequency ≥2 times/week, and ≤6 times/day.Patients agreed to join this study, and signed informed consent.

#### 2.4.3. Exclusion criteria.

Patients who have undergone coronary artery bypass surgery.Patients with other serious diseases (such as severe cardiopulmonary dysfunction, tumor, etc.) or alanine transaminase, aspartate aminotransferase or Cr reaching 1.5 times of the normal upper limit.^[21]^Patients with other diseases that may increase the risk of bleeding (such as cerebral hemorrhage, upper gastrointestinal bleeding), the platelet count decreased, coagulation dysfunction, etc.Pregnant, preparing for pregnancy or lactating women.Patients are allergic to the use of drugs in the study.Participated in or are participating in other clinical trials in the past 1 month.

### 2.5. Study design

Participants will be divided into a treatment group or control group in a 1:1 ratio by a central network-based randomization tool in this study. Independent statisticians will generate random sequences using SAS 9.3 software (SAS Institute, Cary, NC). When the research assistant enters the patient information on the tablet computer, he/she will be assigned a random number and complete the randomization according to the result of the assignment. Before the end of the study, all persons will be blinded to the group assignment, including the researchers and the patient.

### 2.6. Intervention measures

According to the 2014 American College of Cardiology/American Heart Association Guidelines for the Diagnosis and Treatment of Non-ST-Segment Acute Coronary Syndrome, all patients will receive dual antiplatelet therapy (aspirin 100 mg/days + clopidogrel 75 mg/days) and unfractionated heparin, and statins, angiotensin-converting enzyme inhibitors, β-blockers, and nitrates according to the guidelines.^[22]^ All these basic treatments will be recorded in detail in the patient’s medical records and case report forms (CRFs).

The treatment group will orally take Xuefu Zhuyu Granules (Chenpai Pharmaceutical, Jiangsu, China), 1 bag/time, 3 times/day. The control group will orally take Xuefu Zhuyu Granules mimic (Xingreen Pharmaceutical, Sichuan, China, its appearance and taste are the same as Xuefu Zhuyu Granules), 1 bag/time, 3 times/day. Patients in both groups will receive the standard of treatment for 12 weeks.

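### Section 2.6 gives every patient an acute-coronary-syndrome antithrombotic regimen, but the printed eligibility criteria do not require acute coronary syndrome or unstable angina

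*Protocol article*

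**What the plan says.** Section 2.6 bases background treatment on the 2014 American "Guidelines for the Diagnosis and Treatment of Non-ST-Segment Acute Coronary Syndrome". Under it, "all patients will receive dual antiplatelet therapy (aspirin 100 mg/days + clopidogrel 75 mg/days) and unfractionated heparin". Statins, angiotensin-converting enzyme inhibitors, β-blockers and nitrates follow in the same sentence, with a closing reference to the guidelines. The next paragraph describes the granules and the mimic and ends: "Patients in both groups will receive the standard of treatment for 12 weeks".

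Entry is defined in section 2.4. The Western diagnosis in 2.4.1 refers to the "Nomenclature and Criteria for Diagnosis of Ischemic Heart Disease formulated by the World Health Organization". Section 2.4.2 asks that patients "Meet the diagnostic criteria of coronary heart disease angina pectoris in traditional Chinese medicine and Western medicine", with at least one stenosis of 50% or more, age 18 to 70, and between 2 attacks a week and 6 a day. It also requires that "Canadian Cardiovascular Society classification of angina pectoris is grade I–III". Section 2.4.3 excludes, among others, "Patients with other diseases that may increase the risk of bleeding". It does not exclude stable angina.

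**The concern.** The treatment rule and the entry rule differ in reach. The treatment rule is written for an acute syndrome and applies to everyone. The entry rule, as printed, is met by a patient with angina and a qualifying stenosis whether or not the presentation is acute. A site that follows both sections literally would give two antiplatelet drugs and heparin to an eligible patient without ACS because the trial text says so, and not because of that patient's diagnosis.

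Two things are at stake. The first is bleeding exposure that trial participation would add for such patients. The second is applicability. The Discussion part of the Abstract wants the result to inform add-on use of the granules in angina of coronary heart disease generally, yet benefit and bleeding would be observed only on top of an ACS regimen.

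**Working it through.** The plan gives no figure on this point, so the main check is a comparison of the sections.

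**1. Does any criterion restrict entry to ACS?**

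| Place | What it requires | ACS or unstable angina required? |
|---|---|---|
| 2.4.1 | Angina of coronary heart disease, by criteria titled for ischaemic heart disease, plus criteria of traditional Chinese medicine | Not stated; the cited criteria are not shown |
| 2.4.2 | Stenosis of at least 50%; age 18 to 70; grade I to III; 2 attacks a week to 6 a day; consent | No; nothing on rest pain, recent onset or worsening |
| 2.4.3 | Exclusions for bypass surgery, serious disease, bleeding risk, pregnancy or lactation, allergy, other trials | No; stable angina is not excluded |
| 2.6 | Guideline titled for non-ST-segment ACS | Only by the guideline's title |

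The Abstract, the Introduction and section 2.1 all name the target as angina of coronary heart disease, without qualification.

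**2. Does another passage supply a basis for treating everyone this way?** The Introduction says that "nitrates, β-blockers, calcium channel blockers, anticoagulants, and lipid-lowering drugs are standard and first-line therapeutic drugs for angina pectoris in coronary heart disease", citing references 7 and 8. That supports anticoagulants as a class. It does not make unfractionated heparin mandatory for each patient, it does not mention antiplatelet drugs, and it is not the source that section 2.6 relies on (reference 22).

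**3. How many patients could be affected?** Section 2.3 plans 52 per group: 41/(1 − 0.20) = 51.25, rounded up to 52, which reproduces the plan's dropout step. The total is 2 × 52 = 104. The share q of enrolled patients without ACS is not given. The number affected is 104 × q:

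| Assumed q | Patients |
|---|---|
| 0 | 0 |
| 0.1 | 10 |
| 0.5 | 52 |
| 0.9 | 94 |
| 1 | 104 |

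The documents give no bleeding rate, so no number of extra bleeds follows.

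**4. What would a diagnosis-dependent regimen cost the comparison?** If background therapy follows diagnosis, the ACS share p could differ between arms by chance. Section 2.5 describes no stratification. With 52 per arm, the difference stays within 1.96 × √(2p(1 − p)/52) in about 95% of randomisations:

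- p = 0.5: 1.96 × 0.0981 = 0.192, or 19.2 percentage points (10.0 of 52 patients). This is the maximum.
- p = 0.2 or 0.8: 15.4 points (8.0 patients).
- p = 0.1 or 0.9: 11.5 points (6.0 patients).

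An exact hypergeometric check with 52 ACS patients among 104 gives probability 0.97 for a difference of at most 10 patients.

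**The case against.** The strongest reply is that the intended population may well be ACS. The choice of guideline in 2.6 points that way, the diagnostic criteria cited in 2.4.1 are not shown and might narrow entry, and a journal article shortens eligibility lists. On that view the defect is one missing label. This stands as a limit on size: a reader might infer that stable patients will in fact be enrolled, and the documents do not show that. The Introduction does cite evidence in stable coronary heart disease, but as background and not as an entry rule. The reply does not remove the point, because 2.6 is an affirmative rule for every patient and nothing printed restricts entry to match it.

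A second reply is that treatment is guideline-directed throughout, so clinicians would adapt it. The Abstract and section 2.1 do speak of guideline recommendations. In 2.6, however, the closing reference to guidelines most naturally attaches to the statins and the drugs listed after them. Even if it reaches further, the guideline meant is still the ACS one.

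Third, no passage says that heparin or dual antiplatelet therapy is unwarranted without ACS, and the Introduction favours anticoagulants as a class. Absence from an introductory list is no proof that a drug is not indicated. What remains is that the protocol mandates the combination for all on a basis that does not visibly cover all.

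Fourth, the bleeding exclusions in 2.4.3 and the checks for bleeding spots and ecchymosis in 2.8 lower the risk. They do so without supplying an indication.

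Finally, a uniform background is a legitimate choice for a trial of this size, and the conditional regimen gives some of that up.

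**Conclusion.** The point holds as a mismatch between sections 2.4 and 2.6 that should be resolved before patients are treated under this text. Any eligible patient without ACS would receive an ACS antithrombotic regimen, with added bleeding exposure, under a guideline whose title does not cover that patient. The size is unknown and may be near zero if only unstable angina is meant.

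This rests on three assumptions: that the cited diagnostic criteria do not themselves restrict entry to ACS, that the guideline's scope is what its title says, and that heparin added to two antiplatelet drugs increases bleeding exposure.

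Two stronger readings are not supported. A reader might infer 12 weeks of heparin from the sentence on treatment duration. That sentence closes the paragraph on granules and mimic and speaks of standard treatment in general, and heparin's own duration is not stated. A reader might also infer that the treatment effect is biased. It is not: the background rule is the same in both randomised, blinded arms, so the issue is patient safety and applicability.

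**What to change.** Replace the rule in the first sentence of 2.6 with wording such as:

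> All patients will receive standard Western medicine according to the guidelines for coronary heart disease [7,8], with antiplatelet and anticoagulant drugs as indicated for the patient. Only patients diagnosed at enrolment with non-ST-segment acute coronary syndrome (including unstable angina) will receive the regimen of the 2014 guideline [22], including aspirin 100 mg/day, clopidogrel 75 mg/day and unfractionated heparin.

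Record that diagnosis in the case report form beside the basic treatments already entered there, and report ACS status and background drugs by arm.

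The cost is one reworded passage, one form entry, one table and the ethics approval that 2.9 already requires for amendments. Sample size, visits and outcomes do not change. The downside is a background that differs by diagnosis, with the chance imbalance worked out above; the by-arm table makes it visible.

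If only ACS patients are intended, keep 2.6 and add to 2.4.2 a criterion such as: *diagnosis of non-ST-segment acute coronary syndrome (including unstable angina) at screening*. That keeps the background uniform but narrows recruitment. The sponsor has to say which population is meant, since the two remedies are alternatives.

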### 2.7. Outcomes

Cardiac function indexes: left ventricular end-diastolic diameter, left ventricular end-systolic diameter and left ventricular ejection fraction will be measured by color doppler ultrasonic diagnostic apparatus (GE-VIVID7, US).Blood lipid levels: Fasting veins of the patients will be collected in the morning before and after treatment and during follow-up, and blood lipid index, including total cholesterol; triacylglycerol; low-density lipoprotein cholesterol and high-density lipoprotein cholesterol, were measured by an automatic biochemical analyzer (HITEC-7100, Japan).Number of angina attacks per week, total amount of nitroglycerin tablets taken during the study.

We will collect the above outcome measures at baseline, at the end of treatment, and at the 6th, 12th and 24th week of follow-up.

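### The tests named for the four lipid outcomes use no covariate, although baseline lipids may be on-statin in some patients and off-statin in others; this costs precision, not validity

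*Protocol article*

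**What the plan says.** All from the protocol article.

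- **Background treatment (2.6).** All patients receive antiplatelet drugs and heparin, and "statins, angiotensin-converting enzyme inhibitors, β-blockers, and nitrates according to the guidelines". No statin start rule or stable-dose period is given. On recording: "All these basic treatments will be recorded in detail" in the medical records and CRFs.
- **Eligibility (2.4.2, 2.4.3).** Earlier statin use is neither required nor excluded.
- **Randomisation (2.5).** Allocation is 1:1 and no stratification factor is named.
- **Outcomes (2.7).** There are nine efficacy measures: three echocardiographic, two on symptoms ("Number of angina attacks per week, total amount of nitroglycerin tablets taken during the study") and four lipids ("total cholesterol; triacylglycerol; low-density lipoprotein cholesterol and high-density lipoprotein cholesterol"). They are collected at baseline, at the end of treatment and at three follow-up visits.
- **Analysis (2.10).** Two-group comparisons use a t-test or a non-parametric test. For repeated data: "If the data at multiple time points are normal and have homogeneous variance, the analysis of variance will be used", and otherwise generalised estimating equations. No covariate is named, and it is not said whether end-of-treatment values or changes are compared.
- **Hypothesis (Introduction, Discussion).** Both sections attribute a lipid-lowering action to the granules.

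**The concern.** Suppose two patients enter with the same LDL. One has taken a statin for years and the other starts one at entry. By the end of treatment the second is expected to have a much lower value for reasons unrelated to the granules. Any analysis that contrasts later visits with baseline treats that fall as unexplained variation unless it knows who started. Adjusting for baseline LDL helps, but it cannot remove all of this variation because the baseline value means different things in the two kinds of patient.

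At stake is the chance of detecting a modest lipid effect, which the article itself expects, in a small trial whose sample size was built on ejection fraction and not on lipids.

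**Working it through.** **1. The plan's own figure.** Section 2.3 gives ejection fraction 54.74 ± 11.17 against 48.58 ± 10.98, a difference of 6.16. The pooled SD is √[(11.17² + 10.98²)/2] = 11.08. An exact t calculation at 80% power gives 41 per group with a one-sided 0.05 test (52 with a two-sided one), and 41/0.8 = 51.25, rounded up to 52. The sidedness is a separate matter. Only the 41 expected completers per group are used below, with a two-sided 5% test.

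**2. Mechanism, in units of the lipid SD.** Let D be the statin effect, p the share already on a statin at entry, ρ the correlation between baseline and end of treatment, and v = D²p(1−p). Everyone is on a statin by the end of treatment, and statin use at entry is independent of the underlying lipid level. The documents give none of D, p or ρ. The variances are:

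- end-of-treatment value alone: 1
- change from baseline: 2(1−ρ) + v
- adjusted for baseline: 1 − ρ²/(1+v)
- adjusted for baseline and statin use at entry: 1 − ρ²

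With ρ = 0.7 and p = 0.5, power for a 0.5 SD effect with 41 per group is:

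| D | v | Variances, in the order above | Power |
|---|---|---|---|
| 1.0 | 0.25 | 1; 0.85; 0.608; 0.51 | 0.62; 0.69; 0.83; 0.89 |
| 0.25 | 0.016 | 1; 0.616; 0.518; 0.51 | 0.62; 0.82; 0.88; 0.89 |

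Over ρ 0.5–0.8 and p 0.2–0.8, baseline adjustment alone leaves 5–36% excess residual variance at D = 1.0 and 9–64% at D = 1.5. At D = 0.1–0.25 it leaves at most 3%. Simulated type I error was 0.044–0.057 throughout.

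With two visits, the group-by-time test in a repeated-measures analysis of variance is the t-test on change, so the second variance applies to it.

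**3. LDL in mmol/L.** Assumed: off-statin LDL 3.5 ± 0.8, statin reduction 30–40% (SD 10 points), visit noise SD 0.25 or 0.45, 10–60% starting a statin at entry, and a granule effect of 0.2. Residual variances come from 400,000 simulated patients per scenario. Power comes from the noncentral t with noncentrality 0.2/√(2 × variance/41).

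Two scenarios show the steps:

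| Analysis | Noise 0.25, reduction 30%, 20% starters: variance → power | Noise 0.45, reduction 40%, 40% starters: variance → power |
|---|---|---|
| End-of-treatment value | 0.505 → 24% | 0.562 → 22% |
| Change from baseline | 0.340 → 34% | 0.970 → 15% |
| Baseline LDL | 0.233 → 46% | 0.443 → 27% |
| Baseline LDL + statin at entry | 0.144 → 65% | 0.360 → 32% |

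Over all scenarios with 41 per group:

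- unadjusted: 14–44% (end-of-treatment value 20–28%, change 14–44%)
- baseline LDL: 27–54%
- baseline LDL plus statin use at entry: 30–70%

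Within a scenario, the statin term adds about 15–23 points of power at noise 0.25 and about 3–5 points at noise 0.45. A further interaction between baseline LDL and statin use removes 3–8% of the remaining variance at low noise and 0.5–1.6% at high noise.

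**The case against.** **An analysis plan that is not shown may add covariates, and an article condenses.** That is fair, and silence alone would be no finding. But section 2.10 does name the tests, and section 2.6 creates a lipid change that those tests do not account for. The point is a better method than the stated one, not a missing detail.

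**Statin starts need not add variation.** This stands. If everyone is on a statin by the end of treatment, a plain comparison at that visit is not inflated by starts, and section 2.10 does not say whether values or changes are compared. That comparison pays in another way, by discarding the baseline value.

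**Baseline adjustment does most of the work.** This often holds. In step 2 at D = 1.0 it takes power from 0.62 to 0.83, and the statin term then takes it to 0.89. At high visit noise the statin term adds little and power stays low.

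**A reader might infer that a granule effect is hidden on four of the nine outcomes.** The documents do not support that. They give no lipid figures, only LDL was modelled, and where a statin acts weakly on a lipid the loss is negligible.

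**A reader might also infer that a chance imbalance in starters could pass for a granule effect.** With 41 per group, the imbalance has an SD of √[2p(1−p)/41], or 8.8 to 11.0 percentage points for p between 0.2 and 0.8. The test's error rate already allows for it, so there is no added false-positive risk.

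**The data may not be there.** This stands. Section 2.6 says that basic treatments are recorded, but not expressly that use before entry is captured.

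**Conclusion.** The point holds as an avoidable loss of precision in the lipid comparisons. It is not a bias, and type I error is intact. It matters mainly for lipids on which a statin acts strongly.

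The LDL figures in step 3 are illustrative. They rest on the assumed LDL distribution, statin effect, visit noise and share of starters, on everyone being on a statin by the end of treatment, and on statin use at entry being unrelated to the underlying LDL. If every patient is already on a statin at entry, the statin term gains nothing and only the gain from baseline adjustment remains. Even the better model leaves a 0.2 mmol/L effect likely to be missed when visit noise is high. The change is worth making because it is cheap, not because the stated analysis is invalid.

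**What to change.** In section 2.10, state that each lipid outcome is compared between groups in a model containing the baseline value of that lipid and statin use at entry (already on, or started at entry), both fixed before randomisation. An interaction between the two is optional.

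Confirm that the CRF record of basic treatments captures statin use at entry, and tabulate it by group. Do not adjust for statin changes made after randomisation, since these may themselves be affected by treatment.

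The cost is one added sentence, one or two degrees of freedom, and confirming one CRF item. No patient's treatment changes.
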